## Abstract

**Background::**

Molar incisor hypomineralization (MIH) is a change in the formation of dental enamel of systemic origin that affects at least one of the first 4 permanent molars and usually affects incisors. During the eruption, the affected surfaces tend to fracture, exposing the dentin, which causes excessive sensitivity in addition to making the region very susceptible to the appearance of carious lesions. The objective of this research will be to evaluate the clinical effect of antimicrobial photodynamic therapy (aPDT) in permanent teeth with severe and sensitive MIH.

**Methods::**

The methodology will be based on the selection of patients from 6 to 12 years of age with permanent molar teeth, randomly divided in 2 groups. The selected teeth should have MIH on the occlusal surface, indicated for clinical restorative treatment. In Group 1, aPDT will be applied for the treatment of infected dentin. Afterward, the teeth will be restored with high viscosity glass ionomer cement. In Group 2, the removal of the softened dentin around the side walls of the cavity with sharp dentine curettes and posterior restoration with high viscosity glass ionomer cement will be performed. All patients will have clinical and radiographic follow-up with a time interval of 6 and 12 months. The data obtained will be submitted to descriptive statistical analysis to evaluate the association of categorical variables. Chi-square test and Fisher exact test will be applied, to analyze the correlation between the continuous variables, Pearson correlation test will be applied. For the analysis of dentin density in the scanned radiographic images and the microbiological results for colony-forming units, ANOVA and Kruskal–Wallis will be applied.

**Discussion::**

Often in the presence of severe MIH, the presence of dentin sensitivity is also associated with caries lesion, making it even more necessary to respect the principles of minimal intervention.

**Trial registration::**

NCT03904641.

## Introduction

1

The formation of dental enamel occurs through mineral deposition by cells called ameloblasts. Ameloblasts are extremely sensitive and can be affected by systemic factors, which often lead to defects in enamel formation. Depending on the stage of development in which the ameloblasts are affected, different types of changes may occur, such as hypomeneralization.^[1]^ Molar incisor hypomineralization (MIH) is a change in the formation of dental enamel of systemic origin that affects at least one of the first 4 permanent molars and usually affects incisors.^[2,3]^ In the presence of this alteration, the enamel is fragile, porous, and shows areas of white, yellow or brown color, frequently asymmetric. During eruption, the affected surfaces tend to fracture, exposing the dentin, which causes excessive sensitivity, in addition to making the region very susceptible to the appearance of carious lesions.^[4,5]^

A new diagnostic method was developed by Cabral et al in 2019, based not only on the presence, but also on the severity of the MIH. This method is called MIH severity scoring system (MIH-SSS) and is based on the following codes: (0) normal enamel translucency, no enamel opacity; (1) the presence of white/creamy enamel opacity; (2), the presence of yellow/brown opacity; (3) posteruptive breakdown (PEB) restricted to the enamel associated with white/creamy opacity; (4) PEB restricted to the enamel associated with yellow/brown opacity; (5) PEB exposing dentin, the dentin is hard; (6) PEB exposing dentin, the dentin is soft; (7) atypical restoration without marginal defect; (8) atypical restoration with marginal defect; and (9) tooth extracted due to MIH.^[6]^

Due to the clinical characteristics of the teeth with MIH, they become niches of biofilm accumulation. As they also have sensitivity, hygiene is often inadequate, favoring once again the appearance of caries and the eventual involvement of the pulp.^[7]^ Treatment alternatives range from oral hygiene guidance and prevention to restoration, endodontics or extraction, according to the degree of severity of the alteration. The principles of minimal intervention should be taken into account when planning the treatment.^[8]^

Minimal intervention associated with the knowledge of cariology allowed for profound changes in the paradigm of the restorative treatment of caries, since the most striking change involved the principle of maximum preservation of healthy dental structures capable of remineralization.^[9,10]^

Currently, the partial removal of caries, aiming at maintaining pulp integrity, has been considered the therapy of choice in the treatment of deep lesions, provided that certain diagnostic principles are respected.^[10–12]^ In minimally invasive clinical treatment, through different procedures,^[13,14]^ it is recommended to remove the more superficial layer of infected dentin, which is irreversibly denatured and not remineralizable.^[12–14]^ In contemporary dentistry, infected dentin is described with the term “soft dentine” as a concept that defines a softened, often moist tissue that can be easily removed with a curette.^[15,16]^ In the concept of minimal intervention, the selective removal of soft dentine is recommended, that is, it is completely removed from the lateral walls of the cavity, but it is maintained in the pulp wall, in order to avoid pulpal exposure and try to preserve the health of the pulp.^[17]^

The most profound or affected dentin is reversibly denatured, poorly or uninfected, remineralizable and should therefore be preserved. The selective removal of the carious tissue is done, leaving only 1 layer of dentin (a little more hardened) in the deeper portion of the lesion.^[9,17,18]^ Thus, several aspects are important for indicating and performing these procedures, such as a reaction capacity of the dental–pulp complex in front of caries lesion, the initial diagnosis, differentiation of the existing dentin layers into a carious lesion, and the best material indicated for application on the remaining dentin.^[19–21]^

The idea of chemical-mechanical removal of caries consists of the application of a chemical that aims to soften the carious tissue that is removed with a noncutting curette.^[10]^ Papacárie is a gel composed of papain and chloramine. ^[9,22,23]^ Chloramine has properties related to disinfection.^[24]^ Papain is an enzyme similar to human pepsin, which acts as an anti-inflammatory debrisant, not damaging healthy tissue and accelerating the cicatricial process, has bactericidal, bacteriostatic and anti-inflammatory action, and softens the carious tissue facilitating its removal.^[21,24–27]^ By adding methylene blue to the Papacárie formula it can be used in antimicrobial photodynamic therapy (aPDT).^[26,28]^

Antimicrobial photodynamic therapy consists of the use of a photosensitizer that is activated by light and, in the presence of oxygen, produces reactive oxygen species capable of promoting bacterial death.^[29–34]^

## Justification

2

Studies show that aPDT has been widely used in dentistry,^[31–33,35]^ including in the treatment of caries lesions.^[32]^ However, there are few studies in the literature that report the use of aPDT in teeth with hypomineralization. The literature shows that the aPDT with the use of Papacárie associated with methylene blue presents satisfactory results in the treatment of carious lesions in deciduous teeth, with regard to the microbial reduction.^[36]^

The justification for performing aPDT with Papacárie is to promote a conservative and minimally invasive treatment, reducing the risk of pulp exposure in permanent teeth with MIH (Fig. 1).

**Figure 1 F1:**
[figure not shown]
Schedule of enrolment, interventions, and assessments of the present study.

## Methods/design

3

### Objectives

3.1

#### General objectives

3.1.1

To investigate the application of Photodynamic Therapy (PDT) in permanent teeth with severe molar incisor hypomineralization, with painful sensitivity, associated with the presence of caries lesion. PapacárieMblue,^[28]^ modified with the addition of methylene blue as a photosensitizer, in conjunction with the low-power laser for laser therapy will be used for desensitization and decontamination of the cavities.

#### Specific objectives

3.1.2

To compare the use of aPDT with ART.

Hypothesis (H1): The application of Photodynamic Therapy (PDT) in permanent teeth with severe molar incisor hypomineralization, with painful sensitivity, associated with the presence of caries lesion is effective for desensitization and decontamination of the cavities.

Hypothesis (H0): The application of Photodynamic Therapy (PDT) reduces the number of viable bacteria, but is not effective in the treatment of painful sensitivity.

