#### Interventions

3.1.7

##### Group 1

3.1.7.1

1.Initial interproximal radiography;2.Relative insulation (lip retractor, cotton roller, and saliva sucker);3.Taking the VAS scale for pain as responded by the volunteer;4.Microbiological outlet with an otoscopic curette to standardize the volume of carious tissue;5.Application—(PapacarieMblue), leave action for 20 seconds and remove the softened carious tissue just around the sidewalls of the cavity with blunt dentin spoons. Wait another 3 minutes to act on the blue dye present in the gel composition;6.Radiate with the low power laser (single point), following the parameters described in item 3.1.10;7.Clean with cotton ball and water;8.Second microbiological outlet with curette of remaining dentin tissue;9.Clinical evaluation by inspection of remaining dentin texture with rounded probe exploratory probe;10.Clean with cotton ball and water again;11.Sealing the cavity with glass ionomer cement (Riva Self Cure/HV - SDI);12.Taking VAS for Pain Responded by Volunteer;13.Preservation;14.Radiographic control 6 and 12 months.

##### Group 2

3.1.7.2

1.Initial interproximal radiography;2.Relative insulation (lip retractor, cotton roller, and saliva sucker);3.Microbiological outlet with an otoscopic curette to standardize the volume of carious tissue;4.Removal of the softened dentin dentine around the lateral walls of the cavity with sharp dentine curettes # 17;5.Second microbiological outlet with dentin curette;6.Clinical evaluation by inspecting the texture of the remaining dentin with exploratory catheter;7.Clean with cotton ball and water;8.Sealing the cavity with glass ionomer cement (Riva Self Cure/HV - SDI);9.Preservation;10.Radiographic control 6 and 12 months.

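### H1 credits photodynamic therapy, but the two arms compare a whole procedure with ART, so any effect of photoactivation cannot be separated from the rest

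*Protocol article*

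**What the plan says.** All references are to the protocol article.

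- **Hypothesis and objectives.** The specific objective (3.1.2) is "To compare the use of aPDT with ART". H1 in the same section says that PDT in permanent teeth with severe, painful MIH "associated with the presence of caries lesion is effective for desensitization and decontamination of the cavities". The general objective (3.1.1) also opens with PDT, but goes on to say that PapacárieMblue "in conjunction with the low-power laser for laser therapy will be used for desensitization and decontamination of the cavities".
- **What PDT means.** The Introduction describes antimicrobial PDT as a photosensitizer that light activates and that, with oxygen, yields reactive species that kill bacteria.
- **What the gel contains.** The Introduction states that "Papacárie is a gel composed of papain and chloramine". Methylene blue is added so that it can serve in PDT. Of the two base ingredients, "Chloramine has properties related to disinfection" and papain "has bactericidal, bacteriostatic and anti-inflammatory action, and softens the carious tissue facilitating its removal".
- **The arms.** In 3.1.7.1, Group 1 gets the gel, after which the operator is to "remove the softened carious tissue just around the sidewalls of the cavity with blunt dentin spoons", and then laser. In 3.1.7.2, Group 2 has softened dentine removed "around the lateral walls of the cavity with sharp dentine curettes # 17", with neither gel nor laser. Section 3.1.9 labels Group 1 as PDT plus ART and Group 2 as ART.

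**The concern.** The label PDT plus ART suggests that the arms share a common ART and differ only by PDT. The step lists show that they differ in more than that, and some of the extra components have antimicrobial action by the protocol's own account. If the trial finds less sensitivity or fewer colonies in Group 1 and reports this under H1 as worded, readers will take it as evidence that light-activated decontamination or desensitization works. The trial would have shown only that the complete procedure did better than ART. This touches the primary outcome (VAS, 3.1.12) and the CFU outcome alike, and it would remain if every step of the Group 1 procedure were fully fixed.

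**Working it through.** This is a question of what the contrast contains, so the check sets the arms side by side.

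| Component | Group 1 | Group 2 | Source | Part of PDT as the Introduction defines it? |
|---|---|---|---|---|
| Papain and chloramine | yes | no | 3.1.7, 3.1.9, Introduction | no |
| Methylene blue plus 660 nm light in the cavity | yes | no | 3.1.7, 3.1.9, 3.1.10 | yes |
| Excavation instrument | blunt spoons (3.1.7.1); curette (3.1.9) | sharp curettes (3.1.7.2); curette (3.1.9) | sections disagree | no |
| Cotton and water clean before the second CFU sample | yes (step 7, sample at step 8) | no (sample at step 5, clean at step 7) | 3.1.7 | no |
| Laser on the vestibular root, intended against sensitivity | yes | no | 3.1.9 only | no: the gel is described as placed in the cavity, and no photosensitizer is described at the root |

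As a simple additive picture, for illustration only, the expected differences between the arms are:

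- CFU: Δ = gel base + instrument + photoactivation + clean before sampling
- VAS: Δ = gel base + instrument + photoactivation + root laser

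The clean is left out of the VAS line because both arms are cleaned before the restoration and the second VAS follows it. The root laser is left out of the CFU line because it is applied outside the cavity. If the sections are reconciled to one instrument for both arms, that term drops out, and three remain on each line.

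Each line is one equation with several unknowns. A two-arm trial estimates Δ and nothing else. With 24 teeth per group, or any larger number, Δ becomes more precise, but its parts do not become separable.

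Other features that might have separated them:

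- **Arms.** There is no arm with gel and no light, light and no gel, or sham light.
- **Sampling within Group 1.** In 3.1.7.1 the first sample precedes the gel, and the second follows gel, excavation, laser and cleaning. No sample lies between excavation and laser, so the light step cannot be isolated within the arm.
- **VAS.** Under 3.1.12 it is taken before removal and again after the glass ionomer is inserted, so it too spans the whole procedure.

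The stated minimum of 16 teeth per group plays no part in this point.

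**The case against.** The strongest reply is that PDT in this protocol simply means the procedure. Section 3.1.1 names gel and laser together, the Justification speaks of PDT performed with Papacárie, and 3.1.2 sets PDT against ART. A new procedure against a standard one is a legitimate two-arm question, and the Justification gives a package aim: conservative, minimally invasive treatment. Much of this stands. The package comparison is sound, and 3.1.1 already goes most of the way to describing it. What remains is that H1 names only PDT, the Introduction defines PDT by light activation, and the Discussion argues for the method partly through the oxygen species produced. The mechanistic reading is therefore invited by the text.

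A second reply is that the instrument difference is uncertain, and that non-cutting removal belongs to the chemo-mechanical technique anyway. That is fair: the difference rests on 3.1.7 alone. The point does not need it, since both sections give the gel to Group 1 only.

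A third reply is that an analysis plan or the results paper could add the caveat. An analysis plan cannot separate components that always occur together, and the hypothesis is fixed here.

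A reader might also infer that lower VAS or CFU in Group 1 is to be expected from the gel and a gentler instrument even if the laser did nothing. The documents do not support this. They do not call the blunt spoons gentler, say that spoons lower CFU, or say that the gel lowers response to an air jet. They support only that such a difference could arise this way.

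**Conclusion.** The point holds as a mismatch between H1 and the contrast tested. As worded, H1 claims more for PDT than a comparison of the full Group 1 procedure with ART can show, for both VAS and CFU. The share of any difference due to photoactivation is not identifiable. It might be tempting to write this as a range from 0% to 100%, but that is not a proper bound: components acting in opposite directions could put the share outside it.

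Nor does it follow that the trial is invalid or needs another arm. Randomization still supports a conclusion about the whole procedure, which fits 3.1.1.

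The conclusion rests on the Introduction's account of papain and chloramine, on the step order in 3.1.7, and, for the root laser, on 3.1.9 alone. It does not assume that any of the other components has an effect of a given size. The change should be made, because it decides what the trial may conclude.

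**What to change.** In 3.1.2, and in 3.1.1 for consistency, restate the hypothesis as the contrast tested, for example:

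> In permanent molars with severe, sensitive MIH and dentine caries, PapacárieMblue-assisted caries removal with 660 nm laser, then glass ionomer restoration, is compared with curette-only ART and the same restoration, for VAS sensitivity and CFU. Conclusions concern the whole Group 1 procedure; effects will not be attributed to photodynamic activation as such.

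H0 also refers to PDT alone and needs the same terms. Sections 3.1.7 and 3.1.9 must be reconciled on the excavation instruments and on the vestibular-root laser. If the root application is kept, name it in the hypothesis, because it is aimed at the primary outcome. When CFU is reported, state that cleaning precedes the second sample in Group 1 only, if that order stands.

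The downside is a narrower claim. No extra patients, arms or procedures are needed.

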#### Type of study

3.1.3

A randomized and blind controlled clinical trial will be conducted.

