#### Experimental groups

3.1.9

Forty-eight teeth of healthy 6 to 12-year-old children of both genders, without distinction of race or ethnicity in the clinic of the dentistry course of Nove de Julho University (São Paulo, Brazil) will be select.

The participants will be allocated in the experimental groups as follows:

Group 1—PDT + atraumatic restaurative treatment (ART) (n = 24): for the PDT the PapacarieMblue (Fórmula e Ação) will be used. It will be left for 5 minutes in the cavity. The carious tissue will be removed and the application of the PapacarieMblue will be repeated. The tissue will then be irradiated in a single spot with a red laser, of wavelength of 660 nm, for 60 seconds, with the energy of 6J. These parameters were also applied in the vestibular root of the teeth, to try and prevent sensitivity. Laser parameters can be found in item 3.1.10. Selective removal of carious tissue will be made with a curette, followed by cavity cleaning and restoration with Riva Self Cure/HV – SDI.

Group 2—Atraumatic restaurative treatment (ART) (n = 24): Removal of infected dentin with a curette only, followed by cavity cleaning and restoration with Riva Self Cure/HV – SDI.

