#### Evaluation of dentin sensitivity—primary outcome

3.1.12

Before removal of the carious dentin, Group 1 and Group 2 volunteers will respond to the Visual Analogue Scale (VAS),^[38]^ which will obey the following protocol: gauze isolation of neighboring teeth; light air jet in the tooth with MIH for 2 seconds; sensitivity evaluation through the VAS scale. This sequence will be repeated at the end of the procedure, after insertion of the glass ionomer cement.

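### The null hypothesis concedes a bacterial reduction, the alternative is not its complement, and neither names the ART group the trial sets out to compare with

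*Protocol article*

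**What the plan says.** All of this is in the protocol article.

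- **Aim (3.1.2).** The only specific objective is comparative: "To compare the use of aPDT with ART".
- **Alternative (3.1.2).** PDT, in severe and painful MIH teeth with caries, "is effective for desensitization and decontamination of the cavities".
- **Null (3.1.2).** "Hypothesis (H0): The application of Photodynamic Therapy (PDT) reduces the number of viable bacteria, but is not effective in the treatment of painful sensitivity".
- **Design (3.1.3, 3.1.9).** "A randomized and blind controlled clinical trial will be conducted". The arms are "Group 1—PDT + atraumatic restaurative treatment (ART) (n = 24") and "Group 2—Atraumatic restaurative treatment (ART) (n = 24): Removal of infected dentin with a curette only".
- **Primary outcome (3.1.12).** "Before removal of the carious dentin, Group 1 and Group 2 volunteers will respond to the Visual Analogue Scale (VAS"). The measurement is repeated once the glass ionomer cement is in place.
- **Step lists (3.1.7).** Group 1 has a VAS step before and after treatment. Group 2 has none.
- **Analysis (3.1.17).** The significance level is 5%. ANOVA and Kruskal–Wallis are assigned to dentin density and CFU. No test is tied to VAS by name.

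**The concern.** A null hypothesis should describe the absence of the effect under study, and the alternative should cover what remains. Here the null contains a positive claim about bacteria, so rejecting it does not lead to the alternative, and the most ordinary negative result has no place in either statement.

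Both statements also speak of PDT alone. Both arms have softened dentin removed and the cavity sealed before the second VAS, so sensitivity may fall in both for reasons unrelated to PDT. The hypotheses define what will count as success on the primary outcome. If that is written as PDT being effective, with no comparator, a change within Group 1 satisfies the wording without showing that PDT adds anything to ART.

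**Working it through.** **Logic.** Let B mean that PDT reduces viable bacteria and P mean that PDT relieves sensitivity. As worded in 3.1.2, H0 = B and not P; H1 = B and P.

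| Bacteria reduced (B) | Sensitivity relieved (P) | Falls under |
|---|---|---|
| yes | no | H0 |
| yes | yes | H1 |
| no | no | neither |
| no | yes | neither |

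The two hypotheses exclude each other but cover only two of the four states. The complement of H0 is: not B, or P. That is wider than H1. B appears in both, so the pair does not put the bacterial effect in question; the two differ only on pain.

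**Comparator.** The aim in 3.1.2 names ART. H0 and H1 do not, and neither mentions Group 2 or a difference between groups. Section 3.1.14 states a between-group aim for dentin density, but no between-group hypothesis for VAS or CFU is written anywhere in the article.

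**The plan's own figure.** The minimum of 16 teeth per group in 3.1.8 does not bear on this point. It is based on CFU, and its assumed difference and SD are not in the text shown, so it cannot be reproduced.

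**Illustration of the missing comparator.** The only inputs from the document are n = 24 per group (3.1.9) and the 5% level (3.1.17; 3.1.8 uses the two-sided quantile 1.96). The effect is assumed: restoration alone lowers VAS by d_z SDs of the paired differences in both groups, and aPDT adds nothing.

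For a two-sided paired t-test with 23 degrees of freedom the critical value is 2.069 and the noncentrality is d_z × √24 = d_z × 4.899. Power is the probability that a noncentral t exceeds the critical value in absolute size.

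| Assumed d_z | Noncentrality | Chance that the within-Group-1 test is significant |
|---|---|---|
| 0.3 | 1.470 | 29% |
| 0.5 | 2.449 | 65% |
| 0.7 | 3.429 | 91% |
| 1.0 | 4.899 | 99.7% |

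Under the same assumption the true between-group difference is zero, so a valid between-group test at the 5% level is significant in 5% of trials.

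**The case against.** The strongest reply is that the hypotheses stand directly beneath the comparative objective in a randomized controlled trial that assigns VAS to both groups, so the word effective can be taken to mean more effective than ART. That reading is possible and would supply the comparator. It would not repair H0, which would still assert a bacterial benefit and still leave two of the four states uncovered.

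A reader might go further than the text allows in three ways:

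- **That the trial cannot answer its comparative aim.** It can: the arms, the randomization and the VAS in both groups (3.1.12) permit a between-group test.
- **That the bacterial effect cannot be tested.** Dentin is sampled before and after removal in both groups (3.1.7, 3.1.13), and 3.1.17 assigns tests to CFU. Only the wording of H0 presumes the effect.
- **That the authors plan to conclude from a within-group VAS test.** No section says so. The power figures show what the literal wording would permit, not what is planned.

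It is also fair that no joint test of the two-part null is planned, so a rejection of H0 through a failure to reduce bacteria is a formal possibility rather than a likely analysis. Finally, a journal article may leave the VAS test to a fuller document. That is accepted, and the absence of a named VAS test is not counted here. The hypotheses are not omitted; they are stated, and stated wrongly.

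**Conclusion.** The point holds as a fault in the hypothesis statement, not in the design. H0 concedes a bacterial reduction and denies only pain relief, H1 is not its complement, and neither refers to Group 2 although the stated aim is a comparison with ART. This follows from the text of 3.1.2 and needs no assumption.

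The size of the consequence does rest on assumptions. If restoration alone lowers VAS by 0.3 to 1.0 SD of the paired differences and aPDT adds nothing, a within-group test on 24 teeth would support effectiveness in about 29% to over 99% of trials, against 5% between groups. The document gives no VAS difference or SD, so the width of that range should be kept and no single value taken from it.

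The statement should be corrected because it fixes what may be concluded on the primary outcome.

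**What to change.** Replace the two hypotheses in 3.1.2 with:

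- *Primary.* H0: no difference between Group 1 (aPDT + ART) and Group 2 (ART) in post-treatment VAS sensitivity. H1: there is a difference (two-sided 5%).
- *Secondary.* H0: no difference between the groups in post-treatment CFU. H1: there is a difference.

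Preferably adjust each comparison for the baseline value, which 3.1.12 and 3.1.13 already plan to collect. Add one sentence saying that conclusions rest on the between-group contrast and not on change within a group.

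Reconcile the Group 2 step list in 3.1.7, which contains no VAS step, with 3.1.12, which requires VAS in both groups. The primary comparison depends on it.

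The cost is a few sentences of text. If 3.1.12 reflects practice, nothing operational changes. If Group 2 is in fact being treated by the step list in 3.1.7, VAS would have to be collected there, and that should be settled first.
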